
### Data collection

2.9

The data collection will be from the case report forms recorded by the investigator in the trial. The demographic, clinical, and examination results of DED from the participants will be recorded at baseline and during the treatment and follow-up periods. Moderate-to-severe DED will be diagnosed by an experienced ophthalmologist after an ophthalmology examination. The investigator will enter all of the collected data into the case report forms. At baseline, during the treatment period (8th week) and during the follow-up period (32nd week), the forms concerning the questionnaire survey will be completed by the participants under the guidance of a full-time staff member; other forms concerning the ophthalmology examination will be filled in by the investigator according to objective examination results.

### Sample size and statistical analysis

2.10

The sample size calculation is based on the mean SIT value. According to our pilot trial,^[30]^ the decrease in the mean SIT value in the acupuncture group at week 8 is 3.41 ± 3.04. Based on a previous report, the mean value of the decreases in the artificial tear group is 1.8 ± 1.6.^[2]^ We have used PASS Version 11.0 (International Business Machines Corporation, China) software to calculate a sample size of 120 for each group to provide 90% power to detect a difference of 1.61 between the groups with a 2-sided 5% level of significance, allowing for a 20% dropout rate, and with the participants receiving the treatments and completing the follow-up (60 participants in each group).

SPSS Version 22.0 (International Business Machines Corporation, China) software will be used to perform the statistical analysis. Two-sided tests will be used for all statistical analyses. The level of significance is established at 0.05. Efficiency and safety analyses will be based on all participants at randomization according to the intention-to-treat (ITT) principle. All participants who have accepted randomization will be included in the statistical analysis of data. All original data collected from participants in the trial will be included in the statistical analysis. The data cannot be changed or eliminated at random. The missing data in the case report forms will be replaced randomly by the multiple imputation values.^[31]^

We will use the mean and standard deviation (SD) to describe continuous data if the data have a normal distribution and the mean and 95% confidence interval (CI) to describe continuous data if the data are skewed. We will use the percentage or 95% CI to describe categorical data. For comparisons with baseline data, we will use a paired *t*-test for continuous data and a nonparametric test for categorical data. For comparisons of the differences between the 2groups, T-tests or Mann–Whitney *U* tests will be used for comparisons between continuous variables, and chi-square tests or Fisher's exact tests will be used for comparisons between categorical variables, as appropriate. For assessing safety in the trial, the investigator will present the AEs and adverse reactions with tables, which will comprise the categories of AEs, the severity of AEs, the incidence of AEs, and correlation with the treatment. Every participant with serious AEs will stop receiving the intervention. All details will be reported in a timely manner.

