#### Acupuncture group

2.7.1

The treatments will be initiated 1 week after participant randomization. Huatuo Brand stainless-steel needles (0.3 × 40 mm, Suzhou Medical Appliance Factory in China, CL) will be used in the acupuncture group. The acupuncture procedures are performed in accordance with the STRICTA guidelines.^[23]^ Acupuncture will be performed by a trained clinician with > 5 years of experience with acupuncture manipulation. The acupuncture regimen is based on our own clinical experience and pilot trial. The acupuncture point of the bilateral jingming (BL1), which is located on the face, in the depression between the superomedial parts of the inner canthus of the eye and the medial wall of the orbit, will be included in the acupuncture group (Fig. 3). After the participant sits on the chair, the acupuncturist will raise the participant's upper eyelid to expose the medial canthus mound (lacrimal caruncle). The needle will be vertically inserted rapidly into the BL1 point from the medial eyelid to a depth of approximately 0.5 inches. Then, the acupuncturist will vertically lift the needle for 1 minute, and the frequency will be approximately once every 3 seconds. The “deqi” sensation will be induced by lifting acupuncture. At this time, a large amount of tear fluid is expected to flow out of the participant's eyes. The acupuncturist will draw the needle out from the acupuncture point at this time. The treatments will be performed 3 times (Monday, Wednesday, and Friday) per week for 8 weeks and an average interval of 2 days between the 2 adjacent treatments.

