#### Secondary outcome measures

2.8.2

The following secondary outcome measures will be determined.(1)The SIT with anesthesia will be measured at baseline, week 4, and week 32. Tear secretion is an important indicator that reflects tear secretion, and thus, we will also measure the value of SIT with anesthesia during the 32-week follow-up time. The SIT value can reflect the long-term effect of acupuncture on the improvement of tear secretion.(2)The symptoms of DED will be assessed by the participant using a self-administered VAS ranging from 0 to 100 based on recognized DED symptoms (eye dryness, itching, sticky feeling, photophobia, pain, stinging or burning, sandy feeling or grittiness, or a foreign body sensation) at baseline, week 4, week 8, and week 32. The means of these 10 VAS scores will be calculated and used as a global symptoms score.(3)The OSDI will be used to assess the influence of DED on the participant's life at baseline, week 4, week 8, and week 32. The OSDI is a valid and reliable questionnaire and has been used widely in clinical trials.^[25]^ The questionnaire includes 12 problems that reflect vision-related function and environmental stimuli. The total scores will be between 0 and 100. Higher scores represent a more severe dry eye state.(4)The TBUT will be measured at baseline, week 4, week 8, and week 32. The TBUT test is used to assess tear film stability.^[26,27]^ After staining with sodium fluorescein, the first dry spot of the tear film will be observed with a slit lamp and the time of appearance will be measured. The time will be measured repeatedly 3 times, and the average time of the 3 measurements will be the TBUT. A TBUT < 10 seconds will suggest that moderate to severe DED.(5)CFS, which is used to evaluate ocular surface damage and monitor the clinical response to therapy, will be measured at baseline, week 4, week 8, and week 32. Corneal staining will be examined under standard illumination with a slit lamp using a cobalt blue filter and will be graded using the modified Oxford scale.^[28]^(6)To investigate which treatment is preferred, acupuncture or artificial tear acceptance will be assessed at week 8. A 4-point scale will be used, with 1 representing “very difficult to accept,” 2 representing “difficult to accept,” 3 representing “easy to accept,” and 4 representing “very easy to accept.”^[29]^(7)AEs will be assessed using a questionnaire at the end of the treatment and follow-up periods. All participants will be requested to report AEs during the treatment and follow-up periods. All AEs will be assessed for severity (mild, moderate, severe) and seriousness by the investigator.

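### Safety is placed on all randomised participants, and the imputation rule does not except adverse events, so never-treated people can enter the adverse-event denominator

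*Protocol article*

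**What the plan says.** All references are to the protocol article.

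- **Analysis population** (Sample size and statistical analysis): "Efficiency and safety analyses will be based on all participants at randomization according to the intention-to-treat (ITT) principle". The next sentence repeats the rule without any condition on having been treated: "All participants who have accepted randomization will be included in the statistical analysis of data".
- **Missing data** (same section): "The missing data in the case report forms will be replaced randomly by the multiple imputation values". The sentence is not limited to efficacy outcomes.
- **What the forms hold** (Data collection): "The investigator will enter all of the collected data into the case report forms".
- **AE collection** (Secondary outcome measures): "AEs will be assessed using a questionnaire at the end of the treatment and follow-up periods". Participants are also asked to report AEs during both periods, and the investigator grades severity and seriousness.
- **AE reporting** (Sample size and statistical analysis): tables covering "the categories of AEs, the severity of AEs, the incidence of AEs, and correlation with the treatment". Imputation is not mentioned there.
- **Timing** (Acupuncture group): "The treatments will be initiated 1 week after participant randomization".
- **Openness**: under Randomization and blinding, the envelope is opened after consent and the assigned treatment is then offered. The limitations paragraph of the Discussion says that participants cannot be blinded.

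**The concern.** For efficacy, keeping everyone in the arm to which they were randomised protects the comparison. For safety it can work the wrong way, because a person who never received the treatment cannot have an AE caused by it, yet still adds one to the denominator. The incidence then understates what happened to the people who were treated.

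The design leaves room for this. A participant learns the allocation when the envelope is opened and, in the acupuncture arm, has a week before the first session. The protocol does not leave the safety population to a later document; it names safety and assigns it to the randomised set. A statistical analysis plan that used a treated-only set would depart from the protocol.

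The imputation sentence raises a second question. AE entries are collected data and so belong in the case report forms. A participant who withdraws may lack an AE questionnaire, and that is missing case report form data. Taken literally, the rule would supply a value. An imputed event would have no investigator's judgement of severity or of relation to treatment, so it does not belong in the planned tables.

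At stake is the AE incidence by arm, in a trial whose Discussion names safety as an aim alongside efficacy.

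**Working it through.** **Arm size.** The AE denominator under the stated rule is the number randomised per arm. From the article: difference 1.61, SDs 3.04 and 1.6, two-sided 5% level, 90% power, 20% dropout.

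- Mean variance = (3.04² + 1.6²)/2 = (9.2416 + 2.56)/2 = 5.9008.
- n per arm = 2 × (1.960 + 1.2816)² × 5.9008 / 1.61² = 47.84, so 48.
- With dropout: 48 / 0.80 = 60 per arm.

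This reproduces the article's 60 per group. The same sentence also gives 120 for each group, which these inputs do not produce. That is a separate matter; I use 60.

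**Assumed inputs.** The documents give neither the number never treated (u, with f = u/60) nor an AE rate. I take u = 0, 3, 6 and 12, where 12 = 20% of 60 is the entire dropout allowance. For illustration I take an AE rate among treated participants of p = 15%.

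**Reading A: never-treated participants are counted as event-free.** Reported rate = p × (60 − u)/60 = p × (1 − f).

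| u | f | Share of the true rate reported | Reported rate if p = 15% |
|---|---|---|---|
| 0 | 0% | 100% | 15.0% |
| 3 | 5% | 95% | 14.25% |
| 6 | 10% | 90% | 13.5% |
| 12 | 20% | 80% | 12.0% |

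The relative loss does not depend on p. For scale, 9 events in 60 (15%) have an exact 95% interval of about 7.1% to 26.6%, far wider than the shift of 0.75 to 1.5 points at f = 5% to 10%.

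The same effect on a statement that no event of some kind was seen: the one-sided 95% upper limit is 1 − 0.05^(1/n).

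- n = 60: 4.9%
- n = 57 (u = 3): 5.1%
- n = 54 (u = 6): 5.4%
- n = 48 (u = 12): 6.1%

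**Reading B: missing AE entries are imputed.** Suppose m participants in an arm have no AE data and imputation works at the observed rate p. Expected imputed events = m × p, expected observed events = (60 − m) × p, and the total is 60 × p. The imputed share is therefore m/60.

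| m | Expected imputed events if p = 15% | Share of the arm's total |
|---|---|---|
| 3 | 0.45 | 5% |
| 6 | 0.9 | 10% |
| 12 | 1.8 | 20% |

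Under Reading B the reported incidence is on average p, not (1 − f) × p, but part of it rests on events that nobody reported. A given person is either scored as event-free (A) or imputed (B), so the two effects must not be added.

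**The case against.** The strongest reply has five parts.

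1. **Few may be lost before treatment.** The possibility of needling is disclosed at consent, severe fear of needles is an exclusion, and entrants are chosen as able to complete the study. The number never treated could be zero. This stands: the text creates the exposure to bias but does not show that bias will occur. A reader might infer that more people will leave the acupuncture arm before treatment than the eye-drop arm. That is plausible in an open trial, but no figure in the article supports it.
2. **AEs will not in practice be imputed.** The paragraph on AE tables describes events reported and assessed by the investigator and does not mention imputation. This largely stands. A reader might infer that the plan intends to generate AEs; the documents do not say so. What remains is a general sentence that permits it because it makes no exception.
3. **Understated and invented rates cannot both follow.** Correct. Dilution needs the never-treated to be scored as event-free, and imputation is the opposite treatment of the same people.
4. **Switching arms is largely barred.** The section on the artificial tear group bans other dry eye treatments, including acupuncture, during the treatment period. So misclassification by crossover is not a main argument. Any dry eye treatment is allowed in follow-up while AEs are still collected, so a grouping rule must say that this does not move anyone.
5. **The size is small and recoverable.** At f = 5% to 10% the shift is well inside sampling error, and withdrawals and compliance are recorded (Quality control), so exposed-only denominators can be derived. This lowers the severity. It does not remove the point, because the stated rule still directs the analyst to the wrong denominator.

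**Conclusion.** The point holds in a limited form. The protocol fixes the safety analysis on everyone randomised and writes an imputation rule with no exception for AEs. With open allocation and a week before treatment, this can put unexposed people in the AE denominator.

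The size depends on assumptions that the documents cannot settle. If never-treated participants are scored as event-free, the reported incidence is 95% or 90% of the rate among the treated for f of 5% or 10%, and is unaffected if f is zero. The 80% figure is an extreme bound, because it requires every dropout allowed for to have left before the first treatment. If AE entries are imputed instead, the problem is unreported events in the tables, not dilution.

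Severity is minor to moderate. It concerns the safety tables only; the intention-to-treat rule for efficacy is sound and should stay.

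**What to change.** Amend Sample size and statistical analysis in two places.

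1. Keep the intention-to-treat set of all randomised participants for efficacy. Define a separate safety set: participants who received at least one acupuncture session or at least one dose of the study eye drops, grouped by the study treatment received in the 8-week treatment period. State that treatments used during follow-up do not change a participant's group.
2. Limit multiple imputation to efficacy outcomes, and state that AEs are tabulated as observed. It would help to show, beside each AE table, the number randomised, the number treated and the number with AE data in each arm.

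The cost is a few sentences and no new data, since withdrawals and compliance are already recorded. The one small downside is that safety denominators may be slightly smaller than the numbers randomised. Sample size, efficacy analysis and data collection are unaffected.

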### Inclusion criteria

2.4

The inclusion criteria will be as follows.(1)Individuals will be > 18 years of age and < 60 years of age.(2)Participants will meet the diagnostic criteria of DED.^[22]^ The criteria of moderate-to-severe DED are based on the following ophthalmological tests: a Schirmer-I test (SIT) (with the application of cocaine, a local anesthetic) value <10 mm/5 minutes, a tear film break-up time (TBUT) <10 seconds, and corneal fluorescein staining (CFS) ≥ 1.^[2]^ These ophthalmological tests will be performed by the ophthalmologists who do not know the results of the random allocation.(3)Only the single eye with more severe scores or symptoms will be selected to observe the outcome.(4)Participants who can complete the study, treatment, and assessments will be selected.

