#### Primary outcome measure

2.8.1

The primary efficacy endpoint will be the increase from baseline in the SIT value with anesthesia at week 8. The SIT is a diagnostic method used to measure tear secretion,^[24]^ which is measured using tear secretion test paper (Color Bar Schirmer tear test, Eagle Vision, Inc., TN). First, the ophthalmologist responsible for the SIT will use local anesthesia (Alcaine Alcon, Inc., Texas) to arrest reflex tearing. Then, the participants will be requested to look above the eyes, and the ophthalmologists will place the tear secretion test paper under the lower eyelid. Last, the participants will keep their eyes closed for 5 minutes, after which the length of the wet test paper will be measured. The value of SIT equals the length of the wet portion.

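### The planned within-arm tests against baseline cannot show a treatment effect, because participants and the study eye are selected on the measures being tested

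*Protocol article*

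**What the plan says.** - **Within-arm tests.** Section 2.10, Sample size and statistical analysis: "For comparisons with baseline data, we will use a paired" t-test for continuous data, and a nonparametric test for categorical data. The same section sets two-sided tests at the 0.05 level for all analyses, so these are significance tests and not only description.
- **Between-group tests.** The same section: "T-tests or Mann–Whitney *U* tests will be used for comparisons between continuous variables".
- **Entry criteria.** Section 2.4 requires a SIT "value <10 mm/5 minutes, a tear film break-up time (TBUT) <10 seconds, and corneal fluorescein staining (CFS) ≥ 1".
- **Study eye.** Section 2.4: "Only the single eye with more severe scores or symptoms will be selected to observe the outcome".
- **Primary endpoint.** Section 2.8.1: "The primary efficacy endpoint will be the increase from baseline in the SIT value with anesthesia at week 8". TBUT and CFS, also entry criteria, are secondary outcomes in section 2.8.2.
- **Planning figures.** Section 2.10: "the decrease in the mean SIT value in the acupuncture group at week 8 is 3.41 ± 3.04" and "the mean value of the decreases in the artificial tear group is 1.8 ± 1.6". Both are printed as decreases although the endpoint is an increase. Only their sizes are used here.

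The article describes no second baseline reading taken after selection and used for the change score.

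**The concern.** A single SIT reading contains measurement error. Admitting only readings below 10 mm, and then taking the worse of two eyes, favours readings that are low partly by chance. On re-measurement such readings rise on average with no treatment at all. The paired t-test has zero mean change as its null hypothesis, and here that null is false for an inert treatment. The same reasoning applies to TBUT and CFS, which also have entry limits.

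What is at stake is interpretation. The Introduction speaks of exploring whether acupuncture can promote tear secretion, and section 2.8.2 treats SIT as reflecting its long-term effect. A small within-arm p-value would sit easily beside such statements, yet it mixes any treatment effect with selection. At week 32 it also includes whatever other dry-eye treatment was used, since section 2.7.2 leaves treatment free during follow-up.

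**Working it through.** **1. The plan's own figure.** No figure is given for the within-arm tests, so the sample size is reproduced first.

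- Pooled SD = √[(3.04² + 1.6²)/2] = √5.9008 = 2.429.
- n = 2 × (1.960 + 1.282)² × 5.9008 / 1.61² = 47.8, so 48 per arm.
- With 20% dropout: 48/0.8 = 60 per arm, 120 in total.

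This matches the statement of 60 in each group. The statement of 120 for each group conflicts with it, which is a separate matter. The calculations below use 48 completers per arm.

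**2. The paired test at the planning figures.** Expected t ≈ (mean change / SD of change) × √n.

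- Acupuncture: (3.41/3.04) × √48 = 1.122 × 6.928 = 7.77.
- Artificial tears: (1.8/1.6) × √48 = 1.125 × 6.928 = 7.79.

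Power exceeds 99.99% in each arm. Although the planned means differ by 1.61 mm, the two paired tests give practically the same result. This step needs no assumption about repeatability.

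**3. How selection alone produces a gain.** If only the SIT limit acts, the expected gain with no treatment effect is

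(1 − R) × (population mean − mean of the selected baseline readings),

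where R is test-retest reliability and 1 − R = (SD of change²/2) / SD².

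Example, with an assumed population mean of 8 mm and SD of 4 mm, and measurement error set to the documented SD of change of 3.04:

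- 1 − R = (3.04²/2)/16 = 4.62/16 = 0.289.
- The simulated mean of the selected readings is 6.01, so the gain is 0.289 × (8 − 6.01) = 0.58 mm. The simulation gives 0.59 mm, with SD of change 2.85 after selection.
- Expected t = (0.59/2.85) × 6.928 = 1.43, and a significant improvement occurs in about 29% of arms.

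In the same population with the lower-SIT eye chosen (between-eye correlation 0.5), the simulated gain is 1.02 mm with SD 2.79. Expected t = (1.02/2.79) × 6.928 = 2.53, and about 70% of arms are significant.

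**4. Range over assumptions.** The documents give no SIT repeatability, between-eye correlation or source distribution, so these are assumed. The table gives the chance of a significant SIT improvement per arm at n = 48 with no treatment effect. The nominal value is 2.5% in that direction.

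| Assumptions | Eye chosen by lower SIT | Choice unrelated to SIT error |
|---|---|---|
| Mean/SD 8/4 or 7/3 mm, reliability 0.5–0.9, eye correlation 0.7 | about 34–87% | about 6–38% |
| Mean 6–10, SD 3–4, eye correlation 0.5–0.9, error set to SD of change 1.6 | 23–88% | 5–31% |
| Same, error set to SD of change 3.04 | 60–99% | 9–85% |

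The arms are independent, so the chance that both are significant is the square of the per-arm chance. For the first row this is 0.34² to 0.87², about 12–75%, and 0.06² to 0.38², about 0.3–14%. The nominal value is 0.025² = 0.06%.

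**5. The between-group test.** In no-effect simulations with the same selection, the two-sided between-arm test rejects in 4.2–6.5% of trials, close to 5%. Both arms are selected alike, so the artefact cancels.

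**The case against.** The strongest reply is that the trial's inference does not rest on these tests. Section 2.1 states the aim as efficacy versus artificial tears, section 2.10 powers the trial on a difference of 1.61 between groups, and between-group tests follow directly after the paired tests. Nowhere does the article say that efficacy will be concluded from a within-arm p-value. All of this stands. A reader might infer that the primary comparison is biased or that the authors intend to claim efficacy from single-arm change, and the text supports neither.

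The second reply concerns size. Section 2.4 allows the eye to be chosen by scores or by symptoms. If symptoms decide and are unrelated to SIT error, only the 10 mm limit acts and the artefact can be small. A reader might also infer that regression to the mean alone will often give significance in both arms. That does not hold generally: under the symptom route both arms are significant in only about 0.3–14% of no-effect trials (first row of the table). Nor should the larger simulated gains be set against the artificial-tear change of 1.8 mm. With error matched to that arm's SD of 1.6, the gain is only 0.26–0.69 mm even when the eye is chosen by SIT. This reply limits the size of the artefact but does not remove it, and it leaves step 2 of the working untouched.

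**Conclusion.** The point holds, confined to the within-arm p-values. The plan fixes significance tests whose null is false by design, and at its own planning means and SDs those tests would be significant in both arms regardless of which treatment is better.

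The mechanism is certain given the selection rules, provided that the qualifying reading is also the baseline; no other is described. The percentages are conditional on the assumed repeatability, source distribution, eye correlation and eye-selection rule. They were computed for SIT only, so the extension to TBUT and CFS is by reasoning. The randomised comparison is unharmed. This should be changed, but it does not threaten the primary result.

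**What to change.** In section 2.10, replace the paired t-tests and the nonparametric tests against baseline with descriptive reporting: mean change per arm with a 95% CI and no p-value. Add that within-arm change includes regression to the mean, because the interval carries the same shift as the test. State that efficacy conclusions for SIT, TBUT, CFS, VAS and OSDI rest only on the randomised between-group difference.

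Preferably, adjust that difference for the baseline value already collected. This is a separate change from the planned t-test or Mann–Whitney test and is not needed to cure the present defect.

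The cost is the loss of the within-arm p-values and, if adjustment is adopted, slightly more analysis work. No visits, data or participants are added.

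### The primary change-score comparison is valid but unadjusted; one prespecified ANCOVA on baseline SIT would generally be more precise and would tie the result to the mean difference used for sizing

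*Protocol article*

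**What the plan says.** All references are to the Protocol article.

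- **Endpoint (2.8.1):** "The primary efficacy endpoint will be the increase from baseline in the SIT value with anesthesia at week 8".
- **Between-group method (2.10):** "For comparisons of the differences between the 2groups, T-tests" or Mann–Whitney U tests, as suits the data, for all continuous variables. No ANCOVA, regression or covariate is named anywhere in the article.
- **Within-group method (2.10):** "For comparisons with baseline data, we will use a paired" t-test. This does not compare the arms.
- **Baseline SIT:** it is an entry criterion (2.4, below 10 mm in 5 minutes) and a scheduled measurement (2.8.2): "The SIT with anesthesia will be measured at baseline, week 4, and week 32". Every participant should therefore have a value. Section 2.6 mentions no stratification by it.
- **Sizing (2.10):** "the decrease in the mean SIT value in the acupuncture group at week 8 is 3.41 ± 3.04"; for the control, "the mean value of the decreases in the artificial tear group is 1.8 ± 1.6"; and "90% power to detect a difference of 1.61 between the groups with a 2-sided 5% level of significance".
- **Missing data (2.10):** "The missing data in the case report forms will be replaced randomly by the multiple imputation values".

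**The concern.** A change score is a baseline adjustment with the slope set to 1. When the true slope of week-8 SIT on baseline SIT differs from 1, two things follow. The variance of the treatment comparison is larger than it need be. Also, a chance difference in baseline means leaves a residue in the estimated effect, usually with reversed sign because of regression to the mean. ANCOVA estimates the slope and so deals with both.

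The second named option, Mann–Whitney, addresses whether values in one arm tend to exceed those in the other. That is not the mean difference of 1.61 mm in the sample size calculation. At stake are the width of the primary confidence interval and a clear link between the planned effect and the reported one.

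**Working it through.** **1. The plan's own figure.** Inputs from section 2.10: mean changes 3.41 and 1.8, SDs 3.04 and 1.6, two-sided 5%, 90% power, 20% dropout. The section calls these changes decreases; they are read here as sizes of change.

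- Difference: 3.41 − 1.8 = 1.61.
- Pooled SD: √((3.04² + 1.6²)/2) = 2.429.
- Completers per group: 2 × (1.960 + 1.282)² × 2.429² / 1.61² = 47.8, so 48.
- Randomised per group: 48/0.80 = 60.

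This reproduces the 60 per group in section 2.10. The same sentence also gives 120 per group, which these inputs do not reproduce; that is a separate matter. At 48 completers the SE is √((3.04² + 1.6²)/48) = 0.496. Power is 90.1% by the normal approximation and 89.3% with Welch's t. The sizing is thus for an unadjusted comparison of change scores, and it is adequate for that.

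**2. General variance ratio.** Let s0 and s1 be the SDs of SIT at baseline and week 8, and rho their correlation, with a common slope in both arms.

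- Var(change) = s0² + s1² − 2·rho·s0·s1
- Var(ANCOVA) = s1²(1 − rho²)
- Ratio = 1 − (s0 − rho·s1)² / Var(change)

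The ratio cannot exceed 1. Estimating the slope costs one of 2 × 48 − 2 = 94 degrees of freedom. The article gives none of s0, s1 and rho, so all values below are assumptions.

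**3. Equal SDs (s0 = s1).** The ratio reduces to (1 + rho)/2. Normal approximation with the pooled planning SD:

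| rho | Ratio | SE at 48 per group | Power at 48 | Completers for 90% | Randomised (÷ 0.80) |
|---|---|---|---|---|---|
| change score | 1 | 0.496 | 90.1% | 48 | 60 |
| 0.3 | 0.65 | 0.400 | 98.1% | 32 | 40 |
| 0.5 | 0.75 | 0.429 | 96.3% | 36 | 45 |
| 0.7 | 0.85 | 0.457 | 94.1% | 41 | 52 |

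**4. Smaller baseline SD.** Entry is capped below 10 mm and week 8 is not, so s0 < s1 is plausible.

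| s0/s1 | rho 0.3 | rho 0.5 | rho 0.7 |
|---|---|---|---|
| 0.8 | 0.78 | 0.89 | 0.98 |
| 0.6 | 0.91 | 0.99 | 0.98 |

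A case that also matches the planning SD: s0 = 2, s1 = 3, rho = 0.6 gives Var(change) = 4 + 9 − 7.2 = 5.8 (SD 2.41). The ratio is 1 − (2 − 1.8)²/5.8 = 0.993.

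**5. Chance imbalance.** A baseline difference of D shifts the change-score difference by −(1 − rho·s1/s0)·D. Per 1 mm:

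- equal SDs: −0.7, −0.5 and −0.3 mm at rho 0.3, 0.5 and 0.7;
- s0 = 2, s1 = 3, rho = 0.6: −0.1 mm.

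An imbalance of 1 mm is unlikely. With 60 per group and s0 of 2 to 2.43, the SE of the baseline difference is s0·√(2/60) = 0.37 to 0.44 mm, so 1 mm or more has a two-sided probability of about 0.6% to 2.4%. A one-SE imbalance of 0.44 mm with equal SDs and rho 0.5 shifts the result by 0.22 mm, or 14% of 1.61 mm.

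**The case against.** The strongest reply is that nothing here is an error. Endpoint, sample size and t-test all concern change in SIT. The test is unbiased over randomisation, keeps its type I error and has its planned power. This stands, and it limits the point to an improvement in precision.

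A second reply is that the equal-SD table flatters ANCOVA. This stands too: step 4 shows that the gain can almost vanish. In addition, the planning SDs differ by arm (3.04 and 1.6). Arms randomised from one population would not differ like that at baseline, so a single s0, s1 and rho is a simplification. None of this makes ANCOVA materially worse than the planned test.

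Stronger readings that a reader might infer, and that the document does not support:

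- *Baseline is ignored.* It is subtracted for every participant; only the slope is not estimated.
- *The trial is biased or underpowered.* Step 1 shows about 90% power at 60 per group. The imbalance effect is conditional on the realised allocation and averages to zero.
- *Mann–Whitney seriously inflates type I error.* Simulated rejection with equal means, normal data, SDs 3.04 and 1.6 and 48 per group is 5.7–5.8%, a minor departure.
- *Mann–Whitney cannot be combined with multiple imputation.* The Mann–Whitney probability has an estimate and a standard error, so this is too absolute.
- *The missing rule for choosing between the two tests is itself a fault.* An article may leave that to the full protocol or analysis plan.

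**Conclusion.** The point holds as a worthwhile, low-cost improvement to a method that the article states outright. The planned t-test on change is valid, but it is generally less precise than ANCOVA and leaves part of any baseline imbalance in the estimate. The Mann–Whitney option answers a different question from the one the trial is sized on.

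The saving ranges from 15–35% fewer patients for equal precision (equal SDs, rho 0.7 to 0.3) down to under 1% (s0 = 2, s1 = 3, rho = 0.6). Where the trial falls in that range cannot be settled from the article, because it gives no SD of SIT at either visit and no correlation. The case for the change rests on its small cost and small risk, not on any one figure in the tables.

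**What to change.** In section 2.10, name one primary analysis before outcomes are compared by group:

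- ANCOVA of week-8 SIT (or its change; the treatment estimate is the same) on treatment, with baseline SIT as covariate.
- Heteroscedasticity-robust standard errors, because the planning SDs differ (3.04 against 1.6).
- The adjusted mean difference with its 95% CI, pooled over the planned multiple imputations by Rubin's rules.
- Mann–Whitney kept as a sensitivity analysis only.

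The cost is a few lines of text. Baseline SIT is already collected, no patients are added, and the sample size can stay as it is, since the current calculation is conservative for this model.
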